### Sample size estimation

Sample size estimates were based on current recommended steps for calculating the minimum sample size necessary for prediction model development [28]. We anticipate enrolling approximately 100 football student-athletes at each site in their first year of data collection (with the opportunity for athletes to continue in the study during years 2 and 3). In years 2 and 3, we anticipate enrolling approximately 20 new student-athletes (primarily freshmen and transfers) at each site. This will result in an estimated enrollment of approximately 560 unique student-athletes after 3 years of data collection at each site and approximately 1200 player-years across all sites over the study period. Assuming, conservatively, an HSI prevalence of 15%, 5% attrition beyond graduation and transfer (e.g. season ending injuries), a within-subject correlation of 0.3 across study years, and an R^2^ (proportion of variability explained by model) of 20% we will be sufficiently powered to build an index HSI HAMIR index inclusive of approximately 10–12 candidate predictor parameters. Assuming 20% of the student-athletes who sustain an index HSI will re-injure, we conservatively estimate 180 student-athletes and 36 re-injuries will be available to develop a “re-injury” HAMIR index. Using the same modeling assumptions as for the index HSI, this will allow us to create a risk prediction model with up to 4 prediction parameters. The R package *pmsampsize* was used to estimate sample size requirements.

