Because this is strictly an observational study, we cannot guarantee the same practices will occur across all sites (e.g., rehabilitation protocols, return to sport decisions), nor can we control against major program changes such as coaching and staff turnover across the duration of the study period or differences in practice and competition schedules between sites. However, these issues represent realistic variability in clinical care and sports seasons; we intend to account for site-to-site variability and athlete exposure when developing the HAMIR index. Moreover, each site has agreed to adhere to the same protocol for detailed data collection on injury management, and all MRI and IMU data will be processed at a central location. As is common to prospective cohort studies, there is the potential that we are unable to capture all protocolized timepoints on all enrolled athletes; however, the manual of operations addresses specific policies for site coordinators to follow to minimize potential missing data. Additionally, the study analysis plan proposes to assess any missingness in data collection and will account for it, as appropriate, in the analytic phase. Our ability to create a meaningful recurrent HAMIR index is entirely dependent on the number of recurrent HSIs observed during the study period. Risk factors for re-injury are largely unknown and no objective data are available to guide practitioners on return-to-play decisions following HSI. We estimate only being able to include up to 4 predictive parameters in such an index for recurrent HSI and this may or may not be sufficient to accurately predict re-injury risk. However, this information is urgently needed by practitioners and we will minimally be able to provide a preliminary predictive model that can be further tested as more re-injury data is captured in this population.

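### The 180 athletes projected for the re-injury model miss the 0.05 overall-risk precision criterion (246 needed), and the stated limit of 4 parameters holds only on shrinkage with R² read as Cox-Snell

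*Protocol article*

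**What the plan says.** The Sample size estimation section follows "current recommended steps for calculating the minimum sample size necessary for prediction model development" and adds: "The R package *pmsampsize* was used to estimate sample size requirements". For the index model it assumes 15% prevalence, 5% attrition, a within-subject correlation of 0.3 and an R² given only as "proportion of variability explained by model) of 20" percent. It concludes that about 10–12 candidate parameters are supported.

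For the re-injury model it writes "Assuming 20% of the student-athletes who sustain an index HSI will re-injure", then "we conservatively estimate 180 student-athletes and 36 re-injuries will be available". It carries the index model's assumptions over and concludes that "this will allow us to create a risk prediction model with up to 4 prediction parameters".

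The Discussion repeats the limit ("We estimate only being able to include up to 4 predictive parameters in such an index for recurrent HSI"). It also says "we intend to account for site-to-site variability and athlete exposure when developing the HAMIR index".

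The article does not give the type of R², the shrinkage target, the precision margin for overall risk, or how the correlation of 0.3 entered the calculation.

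**The concern.** For a binary outcome, the pmsampsize requirement is the largest of three sample sizes: one for shrinkage, one for optimism in R², and one for precision of the overall risk. The third does not depend on the number of predictors. If the projected sample falls below it, no parameter count meets the full set of criteria, and a limit of 4 can have come only from part of the calculation.

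The type of R² matters as well. At these outcome proportions an R² of 20% is a much stronger assumption on the Cox-Snell scale than on the Nagelkerke scale, and the number of supportable parameters changes accordingly.

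The re-injury model is one of the article's two specific aims, and this is the only formal statement of what its data can support. A reader will take 4 as backed by a recognised calculation. If it is not, the precision of the baseline re-injury risk is overstated and, on one reading of R², so is the protection against overfitting.

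**Working it through.** **Inputs from the Sample size estimation section.** Re-injury proportion φ = 0.20; n = 180 with 36 events; R² = 0.20, carried over from the index model. Index model: φ = 0.15, 1200 player-years, 560 athletes, 5% attrition, correlation 0.3.

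**Assumed, because the article states no values.** Shrinkage target S = 0.9, optimism limit 0.05, overall-risk margin 0.05 (taken as package defaults), and a design effect of 1 + (m − 1) × 0.3 for m years per athlete.

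**The plan's counts.** 0.15 × 1200 = 180 and 0.20 × 180 = 36, so no attrition has been taken off. With 5% attrition: 0.15 × 1140 = 171 athletes and about 34 re-injuries.

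**R² scale.** The maximum Cox-Snell R² is 1 − exp(2[φ ln φ + (1 − φ) ln(1 − φ)]), which is 0.632 at φ = 0.20 and 0.571 at φ = 0.15. A Nagelkerke R² of 0.20 is therefore a Cox-Snell R² of 0.1265 for re-injury and 0.1141 for the index model.

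**Shrinkage criterion, re-injury model.** n = P / [(S − 1) ln(1 − R²/S)], with R² on the Cox-Snell scale.
- Cox-Snell 0.20: 1 / [0.1 × 0.2513] = 39.8 athletes per parameter. 180 / 39.8 = 4.52, so 4 parameters. This reproduces the plan's figure (160 needed for 4, 199 for 5).
- Nagelkerke 0.20: 66.0 athletes per parameter. 180 / 66.0 = 2.73, so 2 parameters; 4 would need 265.
- Solving for S with P = 4 and n = 180 gives expected shrinkage of 0.91 (Cox-Snell) or 0.86 (Nagelkerke).
- At n = 171 the limits are 4.30 and 2.59, which leaves 4 and 2 unchanged.

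**Optimism criterion.** Same formula with S = R² / (R² + 0.05 × maximum R²). Four parameters need 112 (Cox-Snell) or 117 (Nagelkerke), and 180 passes both.

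**Overall-risk criterion.** n = (1.96/margin)² × φ(1 − φ).
- Margin 0.05: (39.2)² × 0.16 = 245.9, so 246.
- Margin 0.055: about 203. Margin 0.06: 171.
- Achieved margin: 1.96 × √(0.16/180) = 0.058; at n = 171 it is 0.060.

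**Required n for 4 re-injury parameters**

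| R² = 0.20 read as | Shrinkage | Optimism | Overall risk | Largest |
|---|---|---|---|---|
| Cox-Snell | 160 | 112 | 246 | 246 |
| Nagelkerke | 265 | 117 | 246 | 265 |

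Against 180, the shortfall is (246 − 180)/246 = 27% or (265 − 180)/265 = 32%.

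**Index model, for comparison, S = 0.9.** With m = 1200/560 = 2.14, the effective n is 1140/1.343 = 849; with m = 3 it is 1140/1.6 = 712. The maximum parameter counts are 21.3 and 17.9 under Cox-Snell, and 11.5 and 9.7 under Nagelkerke. Read as maxima, 10–12 fits Nagelkerke and 4 fits Cox-Snell. The overall-risk criterion at φ = 0.15 needs 196, so the index model passes it.

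**The case against.** The strongest reply is that the 0.05 margin is nowhere in the article. At 0.06 the requirement falls to 171, which the projected sample meets, and the real loss is a margin of 5.8 points instead of 5.0. That is fair as to size: the shortfall in precision is moderate and does not single out 4 as the wrong count. But the article names the package and states no other margin, so a reader must assume the default, and at the default the criterion fails.

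Three stronger readings are tempting and should not be drawn.

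- *The two budgets require two different meanings of R².* The article gives 10–12 as a number the study can support, not as a ceiling. Under Cox-Snell, 10–12 index parameters need only 398 to 478, so that one meaning satisfies both budgets on shrinkage. Nagelkerke with a target of 0.85 and one record per athlete also gives both figures (11.5 to 12.1 at n = 532 to 560, and 4.35 at 180), though it still fails the 246 criterion.
- *A 4-parameter model will be overfitted.* That follows only under Nagelkerke (0.86). Under Cox-Snell the expected shrinkage of 0.91 meets the 0.9 target.
- *Exposure and site use up all four parameters.* This needs one exposure coefficient and three site indicators. The Planned statistical approach section controls for exposure without saying how, and models institution clustering only if needed. The article commits to no such count.

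The Discussion also calls the re-injury model preliminary and doubts that four predictors will be enough. That caveat concerns whether 4 is sufficient. It still presents 4 as supportable and does not disclose a missed criterion.

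**Conclusion.** The point stands in limited form. With 20% re-injury and the assumed 0.05 margin, 180 athletes do not meet the full pmsampsize criteria for any number of parameters. The limit of 4 is recovered at the 0.9 target only from the shrinkage criterion with R² read as Cox-Snell; read as Nagelkerke, the limit is 2. Because R² is undefined, the article cannot be checked against itself: at a 0.9 target with a design effect for repeated years, no single definition gives 10–12 and 4 both as maxima.

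The 246 result depends on the margin but not on R² or the design effect. The choice between 4 and 2 depends on the R² type and the shrinkage target. The stated capacity of the re-injury model should therefore be corrected as written. The index model's budget is not shown to be wrong.

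**What to change.** In the Sample size estimation section, state the R² type, the shrinkage target, the overall-risk margin and how the within-subject correlation was handled. Apply them to both models and report the required n for each criterion.

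There and in the Discussion, restate the re-injury capacity as follows:
- 180 athletes do not meet the overall-risk criterion at a margin of 0.05 (246 needed).
- The shrinkage-based limit is 4 parameters if R² is Cox-Snell, or 2 if Nagelkerke.
- Any coefficients spent on exposure or site count against that limit.
- The re-injury index is therefore exploratory.

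If a margin other than 0.05 or a target other than 0.9 was used, give it and recompute these figures. The cost is a change of wording and a less favourable stated figure; no extra participants are needed.

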### Planned statistical approach

Univariate and bivariate summary statistics and distributional plots will be examined for all candidate predictor variables to assess modeling and hypothesis testing assumptions; appropriate transformations will be considered. Candidate predictors for the prediction models will include standard demographic and clinical measures, muscle strain during sprinting (mechanical), and muscle morphology (e.g. muscle, scar and edema volume). The HAMIR index prediction models for index HSI injury and re-injury will be constructed using generalized estimating equations (GEE) for binary outcomes with a logit link, and will control for athletic-exposures. The correlation among individuals in repeated years will be accounted for using an appropriately identified correlation matrix structure. Clustering at the institution level will be considered and modeled as necessary. The mechanism for missing data will be assessed during the modeling stage and multiple imputation methods will be considered if necessary. The final risk prediction model will provide predictions of the average estimated risk of HSI (or re-injury) for an athlete given the values of model variables.

We will internally validate the models using standard internal validation criteria for the development of risk prediction models. The overall performance of the models will be assessed using the Brier score and calibration assessed using the Hosmer Lemeshow Goodness of Fit Chi-square, with a value < 20 representing sufficient calibration. We will assess discrimination with the c-statistic, with a value of 0.8 or higher indicative of excellent discrimination. Bootstrapping will be used to assess the potential optimization of the model.

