Despite identification of important structural characteristics in the etiology of HSIs, the translation of these measures into practice has been limited due, in part, to the time and effort required to obtain them. That is, the assessment of muscle and tendon morphology requires manual segmentation of many “slices” of MRIs taken along the length of the thigh, a laborious and time-consuming process. Developing intuitive solutions to increase the adoption of measures of hamstring muscle and tendon morphology in practice is of critical importance for improving HSI prediction models. Similarly, the assessment of running mechanics is currently restricted to laboratory-based environments, which limits its practical utility. The advent of wearable sensors, such as inertial measurement units (IMUs), has the potential to allow for field-based measures of running biomechanics to assist with HSI risk determination. Developing a validated, field-based solution will lead to an increased capability to assess running mechanics and its association with future HSI.

While much attention has focused on identifying factors associated with first-time HSI, the rates of recurrent HSI are high [13, 14]. The impact of a prior HSI on structural and functional characteristics of the hamstrings, which may subsequently predispose to recurrent injury, is largely overlooked. Long-term deficits exist in musculotendon characteristics following HSI including: biceps femoris long head atrophy with compensatory short head hypertrophy; reduced muscle quality with fatty infiltration; and an increase in tendon cross sectional area due to scar tissue rather than tendon-specific hypertrophy [15–18]. These factors contribute to an increase in muscle strain under eccentric loading adjacent to the site of the index injury [17]. Determining the relevance of these changes for modeling risk of recurrent injury is of paramount importance given that prior injury is the most consistently identified risk factor for future HSI [19].

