#### Baseline

At baseline, demographic and clinical characteristics including age, height, weight, playing position, prior HSI and detailed surgical history will be recorded for all participants. Additionally, participants will complete the Hamstring Outcome Score (HaOS) which is a functional patient reported outcome survey specific to their hamstring history (e.g. prior HSI) and hamstring function in training, competition and daily life [24]. Additionally, all participants will undergo baseline MRI examinations and testing of on-field sprinting biomechanics and eccentric hamstring strength. Sprinting biomechanics will be paired with MRI data to determine MTU strain. Eccentric hamstring strength of each limb will be assessed during the Nordic hamstring exercise [23, 25].

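### The yearly GEE should name an independence working correlation, or justify another, because prior HSI and post-injury morphology in later years depend on earlier outcomes

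*Protocol article*

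**What the plan says.** The Planned statistical approach builds both HAMIR models with "generalized estimating equations (GEE) for binary outcomes with a logit link". On repeated years it says: "The correlation among individuals in repeated years will be accounted for using an appropriately identified correlation matrix structure". It names no structure and no selection rule, and it does not rule independence in or out. The purpose is stated as follows (the quote stops one word before the end of the sentence): "The final risk prediction model will provide predictions of the average estimated risk of HSI (or re-injury) for an athlete given the values of model". The target is therefore a population-average risk conditional on current predictor values.

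Candidate predictors include demographic and clinical measures and "muscle morphology (e.g. muscle, scar and edema volume"). Under Baseline, "age, height, weight, playing position, prior HSI and detailed surgical history will be recorded for all participants", and the Hamstring Outcome Score, which covers hamstring history, is completed. Table 1 repeats injury history, this score, strength and MRI at baseline in each of the three years. The Background says that "prior injury is the most consistently identified risk factor for future HSI", and that HSI leaves atrophy, fatty infiltration and scar. Sample size estimation assumes "a within-subject correlation of 0.3 across study years".

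**The concern.** By the document's own account, part of what is measured at the year-2 and year-3 baselines is produced by the outcome of the years before. An athlete injured in year 1 has a prior HSI in year 2 and may show scar or atrophy on the next MRI.

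With such covariates, the choice of working correlation in GEE is no longer only a matter of efficiency. A non-independence matrix combines a later year's predictor with an earlier year's residual, and these two are linked by construction. The estimating equation then need not be centred on the risk given current predictors, which is what the index is meant to deliver. The effect at stake is that of prior injury, which the Background treats as the best-established risk factor. Planning to identify a structure and to account for the correlation invites an exchangeable or AR(1) matrix.

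**Working it through.** **1. The plan's own figures.** Athletes: 4 × (100 + 20 + 20) = 560. Player-years: assuming about 20 leavers per site per year, each site has 60, 40 and 40 athletes with 3, 2 and 1 years, so 4 × (180 + 80 + 40) = 1200. Index HSI: 1200 × 0.15 = 180. The 0.3 works as a design-effect input: 1200 × 0.95 / [1 + (1200/560 − 1) × 0.3] = 849 effective records. With the 20% R² read as Nagelkerke (Cox–Snell 0.114) and shrinkage 0.9, the number of parameters is 849 × (0.9 − 1) × ln(1 − 0.114/0.9) = 11.5, in line with the stated 10–12. The article gives no figure for the prior-HSI effect or its precision.

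**2. Mechanism.** Take two years and let the year-2 predictor be HSI in year 1, x₂ = y₁. Write v = μ(1 − μ). One cross term in the equation for its coefficient is x₂√v₂ · r · (y₁ − μ₁)/√v₁, where r = −ρ/(1 − ρ²) is the off-diagonal element of the inverse working correlation.
- If year-1 risk is 15% for all, E[y₁(y₁ − μ₁)] = 0.15 × 0.85 = 0.1275, which is not zero.
- At ρ = 0, r = 0 and the term drops out. At ρ = 0.3, r = −0.3/0.91 = −0.330 and it stays.
- The other cross term (x₁ with the year-2 residual) vanishes only if x₁ adds nothing to year-2 risk given x₂. The two can offset each other, so theory alone does not fix the sign of the bias.

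**3. Size per unit of ρ.** Simulated set-up: 560 athletes, prior HSI coded as ever, athlete heterogeneity plus a carry-over odds ratio of 2, outcome correlation 0.26. The log odds ratio under independence in a large sample is 1.808.
- Fixing ρ at 0.1, 0.2 or 0.3 shifts it by −0.184, −0.377 or −0.585, about −1.84 per unit of ρ.
- The fitted exchangeable ρ is only 0.033, because prior HSI absorbs most of the correlation. Predicted bias is −1.84 × 0.033 = −0.061; simulated, 1.749 − 1.808 = −0.059.
- The fitted ρ has SD 0.040 across data sets, which adds 1.84 × 0.040 = 0.074. Predicted SD is √(0.200² + 0.074²) = 0.213; simulated 0.215, against 0.200 under independence.
- The mean sandwich standard error is 0.192, against 0.189. The sandwich formula treats ρ as known, so it misses this variation.

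**4. Across set-ups** (1000 data sets each; outcome correlation about 0.3, arising from heterogeneity, heterogeneity plus carry-over, or carry-over alone):

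| Prior HSI coded as | Working correlation | Bias in log OR | Empirical SD | 95% coverage |
|---|---|---|---|---|
| either | independence | −0.03 to +0.01 | 0.18–0.21 | 0.95–0.96 |
| last year | exchangeable | −0.01 to +0.05 | 0.24–0.45 | 0.64–0.87 |
| last year | AR(1) | −0.01 to +0.56 | 0.26–0.37 | 0.27–0.85 |
| ever | exchangeable | −0.09 to −0.04 | 4–8% above independence | 0.91–0.94 |
| ever | AR(1) | −0.06 to −0.03 | 4–8% above independence | 0.91–0.94 |

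At outcome correlation 0.1 with last-year coding, exchangeable bias was −0.12 to −0.14 and SD 0.32 against 0.21. Holding ρ at the planning value 0.3 gave bias of −0.57 to −1.05. In the worst case for prediction, AR(1) gave 51.5% risk after prior HSI where 40.7% was observed; exchangeable gave 41.6% in the same set-up.

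A separate simulation with 560 athletes and 15–17% HSI gave the ranges for exchangeable against independence: root mean squared error 0.21–0.45 against 0.18–0.20, and coverage 0.58–0.93 against 0.92–0.98.

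**5. Selection by QIC** (600 data sets per set-up). With independence, exchangeable and AR(1) as candidates, independence was chosen in 74–95% of data sets and the results matched independence (for example SD 0.222 and 0.222). With only exchangeable and AR(1) as candidates (last-year coding, heterogeneity only), SD was 0.379 against 0.222 and coverage 0.722 against 0.937, while the mean standard error was 0.208 against 0.211.

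**The case against.** The strongest reply is that the article commits to nothing harmful. An appropriately identified structure can be independence, and a condensed article may leave the choice to the analysis plan, which the Discussion mentions. A reader might infer that the plan prescribes a non-independence or data-selected structure, or that selection itself does the damage. The text supports neither, and step 5 shows selection to be harmless when independence is a candidate. That part of the reply stands.

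A reader might also infer that the prior-HSI effect is always attenuated. One set-up did show this (1.57 falling to 1.38 at outcome correlation about 0.29, root mean squared error 0.31 against 0.18). Others show almost no bias, and AR(1) can inflate the effect.

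The size also depends on history coding that the article does not fix. If ever-HSI includes three to four pre-study years (an assumption), exchangeable bias is −0.07 to −0.09 and root mean squared error 0.21–0.24 against 0.19–0.21. Observed over expected is then 1.02–1.03 with prior HSI and 0.95–0.97 without, which is mild. With one pre-study year it is less mild: root mean squared error 0.27 against 0.21, coverage 0.83 against 0.95.

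Scope is limited too. Only outcome-dependent predictors are affected. Prior HSI enters the model by inference from the clinical measures, not by name. The re-injury model was not simulated.

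What remains is that the article states a principle for handling the correlation, that principle points towards structures unsuited to these predictors, and it does not guarantee that independence is considered.

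**Conclusion.** The point holds as a cheap improvement. It is not an error that invalidates the plan. With yearly re-measured predictors that partly result from earlier HSI, independence is the only working correlation guaranteed to target risk given current predictors.

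The consistent result for exchangeable and AR(1) is a less reliable prior-HSI estimate: a slightly to much larger true SD, and intervals that cover too rarely. The loss ranges from slight (ever-HSI with long pre-study history) to serious (last-year coding). The direction of bias is not established in general. Reported standard errors barely change or fall, so the output would not warn the team.

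The 0.3 in the sample size section should not be read as the value the working matrix would carry. Once prior HSI is in the model, the fitted correlation is much smaller.

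The figures rest on the plan's layout and 15% HSI, and on assumptions about how prior HSI is coded and how the year-to-year correlation arises.

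**What to change.** In the Planned statistical approach, replace the sentence on the correlation structure with wording to this effect: the primary GEE uses an independence working correlation with robust (sandwich) standard errors clustered on athlete; any other structure must be justified given predictors that depend on earlier outcomes, and independence is always among the candidates compared. Repeated years are still accounted for, through the clustered standard errors.

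The cost is one sentence and no new data. Some efficiency could be lost for predictors that are constant over years, but none was seen in simulation (SD 0.088 and 0.089 under the two structures).

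### A Hosmer-Lemeshow chi-square below 20 cannot show that the HAMIR models are well calibrated, least of all the re-injury model

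*Protocol article*

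**What the plan says.** All of the relevant text is in the protocol article.

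- **Model** (Planned statistical approach): both models are "constructed using generalized estimating equations (GEE) for binary outcomes with a logit link".
- **Validation** (same section): "We will internally validate the models using standard internal validation criteria for the development of risk prediction models". The Brier score measures overall performance. The calibration criterion is "calibration assessed using the Hosmer Lemeshow Goodness of Fit Chi-square, with a value < 20 representing sufficient calibration". Discrimination is judged by the c-statistic, "with a value of 0.8 or higher indicative of excellent discrimination". The paragraph ends: "Bootstrapping will be used to assess the potential optimization of the model".
- **Size** (Sample size estimation): "approximately 1200 player-years across all sites over the study period" from 560 unique athletes, assuming "an HSI prevalence of 15%, 5% attrition beyond graduation and transfer", a within-subject correlation of 0.3 and an R² of 20%. This is said to support 10 to 12 candidate parameters for the index model. The re-injury model is expected to have 180 athletes, 36 events and up to 4 parameters.

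The text does not give the number of Hosmer-Lemeshow groups or the degrees of freedom. It does not say whether the statistic is computed on the development data or on validated predictions. No calibration slope, intercept or plot is named.

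**The concern.** The plan turns a goodness-of-fit test into an acceptance rule, and three things make that unsafe.

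First, a logistic model evaluated on the data that built it is calibrated almost by construction, so the statistic says little about new athletes. Second, failure to reject is read as positive evidence, although with 36 events there are only about 36/10 = 3.6 per tenth of predicted risk. Third, one cut-off serves two datasets of very different size, and its stringency depends on a group count that is not stated.

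The product is a predicted risk for an athlete. An overfitted model gives risks that are too extreme at both ends. The re-injury index is the exposed one: the Discussion says practitioners urgently need it, while conceding that four parameters may not be enough. A label of sufficient calibration could be attached to it without having been tested.

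**Working it through.** **1. The plan's own figure.** The cut-off of 20 has no derivation to reproduce. The 10 to 12 parameters do, and they show the overfitting target behind the design.

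- Unique athletes: 4 × (100 + 20 + 20) = 560, which is the total over all sites.
- Player-years after 5% attrition: 1200 × 0.95 = 1140.
- Design effect: 1 + (1200/560 − 1) × 0.3 = 1.343. Effective N: 1140/1.343 = 849.
- Maximum Cox-Snell R² at 15% prevalence: 0.571. With the 20% read as Nagelkerke, Cox-Snell R² = 0.20 × 0.571 = 0.114.
- N per parameter at target shrinkage S = 0.9: 1/[(S − 1) ln(1 − R²/S)] = 73.7.
- Parameters: 849/73.7 = 11.5, which agrees with the stated range.

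The article does not state S or the type of R². These are the readings that reproduce its figure. On them, the index model was sized for an expected calibration slope of about 0.9.

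**2. What 20 means.** The statistic is Σ (O − E)²/[E(1 − E/n)] over G groups. It is referred to G − 2 degrees of freedom on development data and to about G on fresh data.

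| Degrees of freedom | Setting | P(chi-square < 20) |
|---|---|---|
| 3 | 5 groups, development data | 0.9998 |
| 8 | 10 groups, development data | 0.990 (p = 0.010) |
| 10 | 10 groups, fresh data | 0.971 |
| 18 | 20 groups, development data | 0.667 |

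The usual 5% cut-off on 8 degrees of freedom is 15.5. Moving to it would not help, because about 95% of noise models would still pass on their own data.

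**3. Pure-noise predictors.** Ordinary logistic fits, independent observations, 10 groups (all assumptions), at the plan's sample sizes and prevalences:

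| Setting | Pass, development data | Pass, bootstrap fit tested in original sample | Pass, new data | Median slope, new data |
|---|---|---|---|---|
| N = 1140, 12 predictors, 15% | 98.9% | 71% | 41% | 0.00 |
| N = 1140, 10 predictors, 15% | 99.1% | 79% | 49% | 0.00 |
| N = 180, 4 predictors, 20% | 99.0% | 85% | 71% | 0.01 |

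Further runs of the re-injury setting on new data gave up to 74%. With 20 groups, the development-data pass rate for N = 1140 falls to 66%. With 1200 player-years from 560 athletes and within-athlete correlation 0.3, it is 92% if predictors are constant within athlete and 99% if they partly vary by year.

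**4. Re-injury models with real signal.** With 180 athletes and four predictors of odds ratio 1.5 each (assumed), about 99% pass on development data. The mean slope in new athletes is 0.83 to 0.86 across runs, and 46% to 50% of models have a slope below 0.8. At the plan's R² of 20% the mean slope is 0.88 (Nagelkerke) or 0.89 (Cox-Snell), with 39% or 30% below 0.8.

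**5. Known miscalibration judged in fresh data.** Pass rates with 10 groups and an assumed linear-predictor SD of 1:

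| True slope | N = 1140 | N = 180 |
|---|---|---|
| 1.0 | 97% | 96% |
| 0.8 | 78% | 92% |
| 0.7 | 44% | 88% |
| 0.5 | 2% | 69% |

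At 180 athletes, a slope of 0.7 passes almost as often as perfect calibration. At index size the rule does detect a slope of 0.5.

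**The case against.** The strongest reply is that the 99% is not a property of the rule as written. It needs 10 groups, development-data predictions and independent observations, and the article states none of these. The sentence sits in a paragraph on internal validation that ends with bootstrapping. On validated predictions, noise passes far less often, and the rule can catch gross miscalibration of the index model. This stands, and the 99% must carry its conditions. But the text does not connect the bootstrap with the Hosmer-Lemeshow rule, and at 180 athletes the rule is weak on either reading.

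It can also be said that any correctly specified logistic model passes about 99% of the time on 8 degrees of freedom, and that detecting noise is the job of the c-statistic. In simulation, noise models had a mean apparent c of 0.58 (index) and 0.60 (re-injury), and none reached 0.8. This is right as far as noise goes. It does not cover a model with real signal that is overfitted, which is the realistic risk.

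The group count, the resampling unit and the handling of imputation can fairly be left to an analysis plan. The acceptance rule itself was not left there; it is stated.

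Three stronger readings are tempting and are not supported:

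- **That the index model will be badly overfitted**, because the imaging and biomechanical measures are numerous. The article states 10 to 12 candidate parameters. With 12 and a Nagelkerke R² of 0.20, the mean slope in new data is 0.91 at 1140 player-years and 0.89 at the effective N of 849.
- **That an apparent c of 0.8 would mostly be optimism.** This depends on which R² is meant. The implied true c is about 0.76 (index) and 0.75 (re-injury) under Nagelkerke, but 0.84 and 0.81 under Cox-Snell. The article does not say which, and even under Nagelkerke the mean optimism is only about 0.01 (0.772 − 0.761 and 0.763 − 0.749).
- **That every application of the rule passes nearly everything.** Steps 3 and 5 show otherwise for validated predictions at index size.

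**Conclusion.** The point holds in conditional form. As written, the criterion cannot support a statement of sufficient calibration. Its stringency is undefined without the group count. On development data with 10 groups it passes about 99% of logistic models, good or useless. On fresh data with 180 athletes it passes 71% to 74% of noise models and about 88% of predictions with a true slope of 0.7. The consequence is greatest for the re-injury index; for the index model the rule has real, if limited, value on validated predictions.

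These figures rest on 10 groups, ordinary logistic fits in place of GEE, independent observations except where stated, and the assumed effect sizes.

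This should be fixed before the models are fitted. It does not invalidate the study: the Brier score, c-statistic and bootstrap are planned alongside, no study conduct depends on the cut-off, and the Discussion presents the re-injury index as preliminary.

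**What to change.** - Remove the chi-square below 20 as the criterion for sufficient calibration. If the statistic is still reported, state the number of groups and the predictions used, and draw no conclusion from a pass.
- Judge calibration by the bootstrap optimism-corrected calibration slope, calibration-in-the-large and a smoothed calibration plot, with intervals. Compare the slope with 0.9, the shrinkage target that reproduces the 10 to 12 parameters.
- Resample athletes rather than player-years, because 560 athletes supply about 1200 player-years.
- Apply the 0.8 label to the optimism-corrected c-statistic, and correct the bootstrap sentence, where optimism is presumably meant.

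The cost is a change of wording and slightly more analysis, since the bootstrap is already planned. No data collection changes. The downside is that the calibration statement may turn out less favourable, particularly for the re-injury model.
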